## Abstract

**Introduction:**

Coronary CT angiography (CTA) derived fractional flow reserve (FFR_CT_) shows high diagnostic performance when compared to invasively measured FFR. Presence and extent of low attenuation plaque density have been shown to be associated with abnormal physiology by measured FFR. Moreover, it is well established that statin therapy reduces the rate of plaque progression and results in morphology alterations underlying atherosclerosis. However, the interplay between lipid lowering treatment, plaque regression, and the coronary physiology has not previously been investigated.

**Aim:**

To test whether lipid lowering therapy is associated with significant improvement in FFR_CT_, and whether there is a dose–response relationship between lipid lowering intensity, plaque regression, and coronary flow recovery.

**Methods:**

Investigator driven, prospective, multicenter, randomized study of patients with stable angina, coronary stenosis ≥50% determined by clinically indicated first‐line CTA, and FFR_CT_ ≤ 0.80 in whom coronary revascularization was deferred. Patients are randomized to standard (atorvastatin 40 mg daily) or intensive (rosuvastatin 40 mg + ezetimibe 10 mg daily) lipid lowering therapy for 18 months. Coronary CTA scans with blinded coronary plaque and FFR_CT_ analyses will be repeated after 9 and 18 months. The primary endpoint is the 18‐month difference in FFR_CT_ using (1) the FFR_CT_ value 2 cm distal to stenosis and (2) the lowest distal value in the vessel of interest. A total of 104 patients will be included in the study.

**Conclusion:**

The results of this study will provide novel insights into the interplay between lipid lowering, and the pathophysiology in coronary artery disease.

## INTRODUCTION

1

Fractional flow reserve (FFR) has emerged as the gold standard for assessment of lesion‐specific ischemia and decision‐making on coronary revascularization.^1^, ^2^, ^3^ It is well documented that revascularization can be safely avoided in lesions with FFR > 0.80, while patients having one or more lesions with FFR ≤ 0.80 may benefit from revascularization.^1^, ^4^ In the FAME‐2 study of patients with coronary artery disease (CAD) and FFR ≤ 0.80, the incidence of the composite endpoint (death, myocardial infarction, and revascularization) was lower in the revascularization than in the medical therapy group (13.9 vs. 27%).^4^ Notably, the driving force for the difference in outcomes was repeat revascularization, while the majority of patients in the medically treated group did not experience any serious cardiac events at 5‐years follow‐up (all‐cause death or myocardial infarction did not occur in 85.9% of the patients).^4^ Coronary CT angiography (CTA) derived FFR (FFR_CT_) is based on standard acquired CT data set postprocessing algorithms with integration of quantitative anatomical, physiological modeling and computational fluid dynamics.^5^ In patients with stable CAD, FFR_CT_ demonstrates high diagnostic performance relative to invasively measured FFR, and in real‐world practice FFR_CT_ may favorably change patient management and outcomes.^6^, ^7^, ^8^, ^9^, ^10^, ^11^, ^12^ Accordingly, in the recent 2021AHA/ACC/ASE/CHEST/SAEM/SCCT/SCMR Guideline for the evaluation and diagnosis of chest pain, it is stated that FFR_CT_ in intermediate‐high risk patients with chest pain and stenosis 40%–90% (mid‐proximal segment on CTA) can be useful for the diagnosis of vessel‐specific ischemia and to guide clinical decision‐making on revascularization (evidence level, 2A).^13^ A negative FFR_CT_ result (>0.80) in patients with intermediate range coronary lesions is associated with favorable clinical outcomes.^10^, ^11^, ^12^ A positive FFR_CT_ result (≤0.80) indicates lesion‐specific ischemia when positive 1–2 cm distal to a stenosis (similar to FFR) or diffuse ischemia when there is no lesion‐specific ischemia but a gradual decline in FFR_CT_ along the length of one or more vessels with distal values ≤0.80 (Figure 1).^10^, ^14^ While patients with lesion‐specific ischemia by FFR_CT_ may be referred to ICA for possible revascularization, patients without a focal FFR_CT_ loss have no focal substrate for coronary intervention, and thus are managed by optimal medical therapy alone.^14^

**Figure 1 clc23895-fig-0001:**
[figure not shown]
Fractional flow reserve (FFR_CT_) interpretation. (A) Lesion‐specific ischemia. There is a loss in FFR_CT_ from 0.92 to 0.80 20 mm distal to the mid‐LAD 60% diameter stenosis (red arrows). The resultant ΔFFR_CT_ is 0.12, while the lowest terminal vessel (diameter > 1.8 mm) FFR_CT_ (d‐FFR_CT_) value is 0.75. FFR_CT_, CT angiography (CTA) derived fractional flow reserve; (B) FFR_CT_ ≤ 0.80 in distal vessel segments (diameter > 1.8 mm). There is a gradual decline in downstream FFR_CT_ values with FFR_CT_ > 0.80 20 mm distal to the mid‐prox LAD stenosis (red arrows) and ≤0.80 in more distal segments with the lowest terminal vessel FFR_CT_ (d‐FFR_CT_) = 0.72. LAD, left anterior descending artery.

Lipid lowering therapy with statins is the cornerstone of contemporary preventive care in patients with CAD. Statin therapy is associated with plaque stabilization through favorable changes in high‐risk atherosclerotic phenotype characteristics (APC) and a lower rate of overall atherosclerotic plaque volume progression.^15^, ^16^, ^17^, ^18^ These changes include a reduction in the total noncalcified plaque burden including low attenuation density plaques (LAP), and stabilization of thin‐cap fibroatheroma. By serial coronary CTA, a significant decrease in APC plaque volumes have been demonstrated over 6–12 months both by regular and potent statin therapy, with more pronounced effects of the latter.^17^ In post‐hoc analyses, the presence and burden of APC plaques, even in nonobstructive CAD, is associated to the presence and severity of ischemia as assessed by FFR.^19^, ^20^, ^21^ One prospective single‐center study of 20 patients with stable CAD treated with fixed‐dose rosuvastatin 5 mg per day for 18 months after coronary stenting suggested the existence of a negative correlation between low density lipoprotein (LDL) cholesterol lowering and changes in FFR.^22^ We designed the prospective, multicenter, randomized FLOWPROMOTE study to investigate, in hemodynamically significant CAD, whether lipid lowering‐induced changes in plaque morphology improves coronary physiology as assessed by FFR_CT_.

## METHODS

2

### Study design

2.1

The FLOWPROMOTE study is an investigator‐driven, proof‐of‐concept, prospective, multicenter, randomized, open‐label trial. The study is registered at www.ClinicalTrials.gov (NCT04737408). Three Danish centers with experience in coronary CTA and FFR_CT_ testing participate in the study (Department Cardiology, Aarhus University Hospital; Department of Cardiology, University Hospital of Southern Lillebælt Hospital; and Department of Cardiology, University Hospital of Southern Denmark, Esbjerg, Denmark). A total of 104 patients will be included in the study. The study protocol has been approved by the Danish Medicines Agency, the Ethics Committee (EudraCT nr. 2019‐001912‐50) and by the research review boards at each participating center. The study is led by a chairman, primary investigator, principal investigators and a steering committee (details are provided in the Supporting Information). Coronary plaque and FFR_CT_ analyses will be analyzed by independent core‐laboratories. Details of the committees, laboratories including members are provided in the Supporting Information.

### Study objectives

2.2

The main purpose of study is two‐fold: (1) to assess whether lipid lowering therapy in stable CAD patients with FFR_CT_ ≤ 0.80 is associated with improvement in coronary physiology, and (2) to investigate whether there is a dose–response relationship between lipid lowering intensity, plaque regression, and coronary flow recovery.

### Study subjects

2.3

Patients referred for nonemergent clinically indicated coronary CTA demonstrating CAD, diameter stenosis ≥50%, FFR_CT_ ≤ 0.80, and no obvious indication for coronary revascularization are eligible for study inclusion (Table 1). In the participating institutions, FFR_CT_ testing is recommended for physiological coronary assessment in patients with stable chest pain and intermediate‐risk anatomy as previously described.^10^ Anatomical and physiological study eligibility criteria are shown in Table 1 and Figure 2. All patients undergoing clinically indicated FFR_CT_ assessment (including reasons for study exclusion) during the study period are registered in a screening list.

**Table 1 clc23895-tbl-0001:** Study eligibility criteria

Inclusion criteria	Exclusion criteria
1. Age >35 years 2. Symptoms suggestive of stable CAD 3. CAD with at least one stenosis with ≥50% lumen reduction determined by the index coronary CTA investigation^a^ 4. Presence of at least two low attenuation plaques (with attenuation <30 Hounsfield units) present in at least two orthogonal planes by CTA 5. Sinus rhythm 6. LDL cholesterol >2.0 mM 7. FFR_CT_ ≤ 0.80 (Figure 2) 8. Life expectancy >3 years 9. Fertile women must use safe contraception throughout the study period	1. Previous lipid lowering therapy^b^ 2. Known CAD 3. Unstable angina 4. Indication for coronary revascularization 5. BMI > 40 6. Allergy to iodinated contrast media 7. Poor coronary CTA image quality inadequate for FFR_CT_ calculation (determined by core laboratory) 8. Pregnancy (women < 45 years will be screened for pregnancy) 9. Moderate to severe liver failure 10. Estimated glomerular filtration rate <60 ml/min 11. Participation in another clinical trial **Anatomical or FFR** _ **CT** _ **based exclusion criteria**: 12. Left main‐ stenosis ≥50%, 3‐VD or high‐grade proximal LAD stenosis resulting in direct referral to ICA 13. FFRct ≤ 0.80 2 cm distal to stenosis on CTA in segments 5 and 6 (Figure 2). 14. FFRct ≤ 0.75 2 cm distal to stenosis on CTA in segments: 1^c^, 7, 11^c^, 12 (ramus) (Figure 2).

Abbreviations: BMI, body mass index; CAD, coronary artery disease; CTA, computed tomography angiography; FFRCT, CTA derived fractional flow reserve; ICA, invasive coronary angiography; LAD, left anterior descending coronary artery; LDL, low density lipoprotein.

^a^
Assessed at the discretion of the CTA reading cardiologist.

^b^
Patients treated with lipid lowering therapy <3 months before the index CTA investigation can be included in the study if meeting inclusion criteria.

^c^
If (co‐) dominant vessel.

**Figure 2 clc23895-fig-0002:**
[figure not shown]
Fractional flow reserve (FFR_CT_) based exclusion criteria. Patients with FFR_CT_ ≤ 0.80 in left main stem, or proximal LAD, and those with FFR_CT_ ≤ 0.75 in a dominant proximal RCA, dominant proximal LCx, ramus or mid‐LAD segment are excluded from this study. LCx, left circumflex artery; RCA, right coronary artery.

### Patient workflow

2.4

Patients randomized to one of two lipid lowering treatment regimens are followed for 18 months (Figure 3). Coronary CTA scans with blinded plaque and FFR_CT_ analyses will be repeated after 9 and 18 months. For assessment of the reproducibility of plaque and FFR_CT_ two CTA scans at a 1 h interval are performed at the 9 months visit. Antianginal and antiplatelet treatments are used at the discretion of the treating physicians. Recurrent angina will be managed according to societal guidelines, including referral to ICA in the event of uncontrolled symptoms.^2^, ^3^, ^13^ In the event of revascularization being performed during follow‐up, patients are encouraged to continue in the study (including the CT imaging protocol for plaque and FFR_CT_ assessments in nonrevascularized vessels).

**Figure 3 clc23895-fig-0003:**
[figure not shown]
Study flow. At the 9 months visit two separate CT angiography scans are performed with a 1 h interval.

### Coronary CT angiography

2.5

CTA is performed using contemporary high‐end technology scanners according to the best practice CTA acquisition guidelines.^23^ Oral and/or intravenous beta‐blockers or oral ivabradine are administered if necessary targeting a heart rate <60 beats/min., and all patients receive sublingual nitrates (spray, 0.8 mg) 3 min before the scan. An initial nonenhanced scan for assessment of the Agatston score is performed. Coronary CTA acquisition using prospective electrocardiographic triggering with 70–140 kV tube voltage depending on patient weight and the calcific burden is recommended. CTA acquisition settings in the index scan are registered for repetition in the follow‐up CTA investigations. Coronary stenosis severity at the index scan is assessed at the discretion of the CTA reading cardiologists. Lesion location is registered in an 18 segment coronary model.^24^ Patients with at least one lesion with ≥50% stenosis severity at the index scan will have FFR_CT_ performed.

### Biochemistry

2.6

Measurement of total cholesterol, high density lipoprotein cholesterol, LDL cholesterol is measured at baseline and at follow‐up visits. Lipoprotein(a) is measured at the baseline visit. Hepatic enzymes, creatin kinase, creatinine, and hemoglobin is assessed at baseline, and after 3 months. Further special analyses related to inflammation for substudy analyses will be performed (Supporting Information).

### Coronary plaque analysis

2.7

Together with the pericoronary adipose tissue (PCAT) attenuation as a marker of coronary artery inflammation, plaque analyses will be performed at a core‐lab in vessel segments with diameter ≥2 mm using a semiautomated software (Autoplaque, Cedars‐Sinai Medical Center) as previously described.^18^, ^19^, ^20^, ^25^, ^26^, ^27^, ^28^ In brief, automated attenuation thresholds will be used for scan‐specific plaque differentiation,^26^, ^27^ and the vessel lumen, wall and plaque are defined automatically with manual input as required. Total plaque, calcified, and noncalcified (including LAP < 30 HU) will be measured (mm^3^), and aggregate plaque volume (APV%) will be computed as total plaque volume/vessel volume × 100%. Plaque burden will be assessed on a per‐lesion (diameter stenosis ≥50%), vessel and patient level. Observers will be blinded to all clinical information, timing of the CT scans and FFR_CT_ results.

**Figure 4 clc23895-fig-0004:**
[figure not shown]
“Total vessel” FFR_CT_, FFR_CT_‐AUC. All FFR_CT_ values at 1 mm intervals from the ostium along the total length of the vessel (including segments with a diameter >1.8 mm) are integrated by using the normalized AUC (FFR_CT_‐AUC) index and hereby assessing the “total vessel” FFR_CT_. The FFR_CT_‐AUC index thus represents the sum of all multiple downstream resistances from both focal and diffuse disease. We hypothesize that LDL lowering will lead to an upward shift of the FFR_CT_ curve and thus an increase in FFR_CT_‐AUC in vessels with CAD. (A) is calculated from case A, and (B) from case B in Figure 1. AUC, area under the curve; CAD, coronary artery disease.

### Randomization and treatment

2.9

Patients are randomized 1:1 to either usual care lipid lowering treatment (atorvastatin 40 mg daily) or to intensive lipid treatment (rosuvastatin 40 mg plus ezetimibe 10 mg daily) for 18 months. We expect that atorvastatin 40 mg will reduce LDL cholesterol with 45%–50% while the combination of rosuvastatin 40 mg + ezetimibe 10 mg is expected to reduce LDL cholesterol with up to 70%.^32^ Study medication is provided to each patient in 3‐month batches and unused medication is returned for assessment of medication adherence. New or residual angina or potential statin side effects are addressed at the 3‐month visits or via a direct telephone line to the research staff in between these visits. Thus, we expect a low rate of study medication nonadherence and low loss of follow‐up. In the event of statin side‐effects, the rosuvastatin dose may be lowered to 20 mg in the intensive treatment arm. If continuing intolerable side effects patients will be withdrawn from their study allocated treatment to no or alternative downstream lipid lowering management according to local practice (observation group). In Denmark, the patients who fulfill the FLOWPROMOTE inclusion criteria have an LDL‐cholesterol treatment goal of <1.8 mM and are recommended treatment with atorvastatin 40–80 mg or rosuvastatin 20 (−40) mg. As atorvastatin 40 mg reduces LDL‐cholesterol by 45%–50%,^32^ we estimate that most individuals in the atorvastatin 40 mg group will reach an LDL‐cholesterol level in the range of 1.5–2.0 mM. In the event that LDL‐cholesterol is considered to be uncontrolled by the treating physician, patients may have their lipid‐lowering treatment intensified. Patients with changes in the assigned study medication during the course of the study will be followed in the observation group. Except for the study directed treatment regimen, the observation group will follow the study protocol according to the intention‐to‐treat principle including CTA studies with blinded plaque and FFR_CT_ analyses.

### Endpoints and substudy analyses

2.10

In our analyses, we will assess whether the changes in FFR_CT_ are associated to the absolute changes in LDL‐cholesterol from baseline until 18 months of follow‐up (ΔLDL‐cholesterol). The primary endpoint will be the 18‐month difference in FFR_CT_ using (1) the FFR_CT_ value 2 cm distal to stenosis in the event of lesion‐specific ischemia at baseline, and (2) the lowest distal value in patients with a gradual nonfocal downstream decline in FFR_CT_ (Figure 1). Secondary endpoints are the temporal difference in ΔFFR_CT_ and FFR_CT_‐AUC, and changes in FFR_CT_ between the two treatment groups. Additional exploratory analyses are outlined in the Supporting Information. Substudies are planned to assess (1) the interscan reproducibility (based on the two CT scans at 9 months, Figure 3) of total and individual plaque volumes, and PCAT attenuation estimates, FFR_CT_, FFR_CT_‐AUC, ΔFFR_CT_, APPROACH_FFRCT_ score and the V/M‐ratio, and (2) the relationship between ΔLDL‐cholesterol, total and LAP volumes, and changes in inflammatory biomarkers, and FFR_CT_ estimates.

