### Data analysis plan

2.12

In the primary intention‐to‐treat analysis plan changes in FFR_CT_ will be compared in a temporal hierarchically fashion. Thus, if the difference in FFR_CT_ estimates at 18 months is of statistically significance, then the difference in FFR_CT_ at 9 months (scan 1) will also be tested. Changes in categorical variables will be analyzed using the Fishers exact test, and means between groups by the Student *t*‐test, Wilcoxon signed rank test or the Kruskal–Wallis test as appropriate. The continuous relationship between variables will be assessed by linear regression supplemented by restricted cubic spline to adjust for nonlinearity as appropriate. Reproducibility assessments will be performed by calculation of standard error of measurement and within‐subject coefficient of variation.

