FFR is invasive and associated with increased risk. Therefore, in this study employing repeated assessments of the coronary physiology, FFR_CT_ is used as a surrogate for FFR. This strategy is supported by several studies demonstrating high diagnostic performance and correlation when compared to measured FFR.^6^, ^7^, ^8^ FFR_CT_ provides simultaneous computation of pressure and flow in the entire coronary tree, thus exposing both lesion‐specific pressure as well as nadir FFR_CT_ values. Low terminal vessel FFR_CT_ values remote from a focal lesion may be due to diffuse CAD and/or reflect the sum of serial flow‐limiting lesions.^14^ In a previous study of real‐world consecutive patients with stable CAD, approximately 50% of those with FFR_CT_ values ≤0.80 deferred from catheterization had low terminal vessel FFR_CT_ positivity.^10^ We hypothesize that both lesion‐specific as well as low terminal vessel FFR_CT_ values ≤0.80 can be increased by lipid lowering therapy. On the other hand, lipid lowering‐induced plaque regression/stabilization with associated improvements in the physiological profile expectedly is not restricted to lesions or vessels with FFR_CT_ ≤ 0.80. To delineate in more detail the total effect of plaque regression on the coronary physiology, we introduce in this study the FFR_CT_‐AUC index which integrates all downstream resistances arising from both focal and diffuse disease. When compared to the terminal vessel FFR_CT_ (also addressing the sum of focal and diffuse disease), FFR_CT_‐AUC may be less susceptible to the potential influence of the small vessel caliber and suboptimal CT resolution on the FFR_CT_ diagnostic accuracy. Thus, relative to traditional FFR_CT_ metrics, FFR_CT_‐AUC may add important information on the impact of lipid lowering therapy on flow both in vessels with or without FFR_CT_ ≤ 0.80 at baseline. The repeated CTA + FFR_CT_ investigation strategy in the FLOWPROMOTE study allows for comprehensive assessment of the temporal interplay between lipid lowering therapy, changes in disease morphology and physiology including new metrics such as PCAT attenuation, V/M ratio and the APPROACH_FFRCT_ score.^25^, ^30^, ^31^

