In the FLOWPROMOTE study, patients are randomized to two different lipid lowering regimens; usual care with atorvastatin 40 mg/day versus intensive lipid lowering with rosuvastatin 40 mg/day plus ezetimibe 10 mg/day. A no‐treatment arm was not included because of the obvious unethical nature of omitting guideline‐directed lipid lowering treatment in patients with documented CAD. The rationale for choosing the two different treatment intensities is to be able to demonstrate a potential dose–response relationship between achieved LDL cholesterol values and improvements in coronary physiology. Such a dose–response relationship would be consistent with previous studies demonstrating that the extent of plaque volume regression is greater in patients who achieve the lowest LDL cholesterol values.^38^, ^39^ Importantly, these previous studies have not indicated that there is a lower LDL threshold beyond which further LDL lowering would not yield additional plaque regression. Accordingly, patients treated with multiple lipid‐lowering agents such as combination therapy of statin and ezetimibe or statin plus PCSK9 inhibition have greater plaque regression than patients treated with statin monotherapy.^40^, ^41^ The FLOWPROMOTE study may therefore be able to provide answers on the potential of imaging to guide personalized lipid lowering strategies based on both the atherosclerosis and physiology phenotype.

Demonstration of a beneficial influence of pharmacological lipid lowering on both the coronary plaque phenotype and concomitant improvements in coronary physiology will expand our understanding of CAD, underscore the importance of lipid lowering in patients with CAD, and potentially in the future have implications for individualized management of patients with lesion‐specific ischemia who may benefit from intensive lipid lowering therapy as an alternative to current interventional practice. If proof‐of‐concept can be demonstrated the present study may form the basis for initiation of large‐scale, randomized trials to assess the safety of deferral ICA and revascularization in subsets of patients with CTA determined flow‐obstructive CAD.

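### If, as it most naturally reads, the primary endpoint is one pooled comparison of focal and diffuse patients, a positive result would not by itself show that both types improved

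*Protocol article*

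**What the plan says.** Section 2.10 calls the primary endpoint, in the singular, the 18-month difference in FFRCT. The measurement site depends on the patient. It is the value 2 cm beyond the stenosis where there is lesion-specific ischemia at baseline, and "2) the lowest distal value in patients with a gradual nonfocal downstream decline in FFR_CT". The Methods paragraph of the Abstract lists the same two values but does not assign them to patient types.

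Section 2.12 describes one comparison at 18 months. If that difference "is of statistically significance", the 9-month difference is tested next. The section does not mention baseline type. Section 2.11 sizes the trial on the lowest distal value only.

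The Discussion states a two-part hypothesis: "We hypothesize that both lesion‐specific as well as low terminal vessel FFR_CT_ values ≤0.80 can be increased by lipid lowering therapy". It later looks ahead to "individualized management of patients with lesion‐specific ischemia who may benefit from intensive lipid lowering therapy as an alternative to current interventional practice". The Introduction says that "patients without a focal FFR_CT_ loss have no focal substrate for coronary intervention". The Discussion also reports that in a previous cohort about half of the FFRCT-positive patients "deferred from catheterization had low terminal vessel FFR_CT_ positivity".

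**The concern.** In the article's own account the two baseline types differ in where FFRCT is read and in what a rise would mean clinically. A pooled mean can move because only one type moved. If the primary result is positive, the Discussion's wording invites the reader to conclude that both types improved, or that lesion-specific ischemia in particular recovered. That second group is the one for which the article raises the possibility of an alternative to intervention. The question is how often a pooled test would be significant when lesion-specific patients had not changed at all.

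**Working it through.** **Inputs from the article**
- Section 2.1: "A total of 104 patients will be included in the study". Section 2.9: "Patients are randomized 1:1 to either usual care lipid lowering treatment". This gives 52 per arm.
- Section 2.11: mean change +0.07 (intensive) and +0.04 (usual care), SD of change 0.03 in both arms, noncompliance 15%.

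**Assumptions**
- Two-sided 5%, because no alpha is stated. This choice reproduces both stated powers.
- The lesion-specific share *s* is not stated for this trial. The earlier cohort suggests about 50%, so I use 30%, 50% and 70%.
- Lesion-specific patients do not change. Diffuse patients change as section 2.11 plans, diluted by 0.85: usual care 0.85 × 0.04 = 0.034, intensive 0.85 × 0.07 = 0.0595, difference 0.0255.
- The within-type SD is 0.03.

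**Reproducing the plan's figure.** With 52 per arm and SD 0.03, a difference of 0.025 gives 98.9% power (normal approximation), and 0.0255 gives 99.0% (noncentral t). The stated 99% is confirmed. The stated 72% reproduces as the power to show an effect above 0.01 when the true effect is 0.025: a net 0.015 gives 72.2%.

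Section 2.10 lists the between-group change as secondary, while section 2.11 powers on it. I therefore ran both readings.

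**(a) Change over time, all 104 patients, every diffuse patient gaining 0.034.** Pooled mean = (1 − s) × 0.034. SD = √[0.03² + s(1 − s) × 0.034²]. The second term is the spread between types.

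| s | Pooled mean | SD | Mean ÷ SE | P(significant) |
|---|---|---|---|---|
| 30% | 0.0238 | 0.0338 | 7.18 | >99.9% |
| 50% | 0.0170 | 0.0345 | 5.03 | 99.9% |
| 70% | 0.0102 | 0.0338 | 3.08 | 86% |

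**(b) Difference between arms, 52 vs 52.** Pooled difference = (1 − s) × 0.0255. The SD in each arm is √[0.03² + s(1 − s) × g²], with g = 0.034 (usual care) or 0.0595 (intensive).

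| s | Pooled difference | Arm SDs | Difference ÷ SE | P(significant) |
|---|---|---|---|---|
| 30% | 0.0179 | 0.0338, 0.0405 | 2.44 | 68% |
| 50% | 0.0128 | 0.0345, 0.0422 | 1.69 | 39% |
| 70% | 0.0077 | 0.0338, 0.0405 | 1.05 | 18% |

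Simulation agrees (about 68%, 39% and 18%). If the SD is held at 0.03, the first two rows become 85% and 57%. That omits the spread between types which the assumption itself creates, so those figures are too high.

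**(c) Precision by type, SD 0.03**
- 52 patients of one type (26 per arm): 95% half-width ±0.008 for change over time and ±0.017 for the arm difference; 85% power for 0.0255.
- 31 patients of one type (15 and 16): ±0.011 and ±0.022; 63% power.
- Significant arm differences in both types, each with a true 0.025 (normal approximation): about 73% at a 50:50 split and 61% at 30:70.

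**The case against.** The strongest case on the other side has five parts, and much of it stands.

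- **Pooling is inferred.** Sections 2.10 and 2.12 do not say that the two components enter one test. This stands. But if two tests are meant, section 2.12 gives no rule for combining them, so the text needs settling either way.
- **A reader might infer that the trial sets out to prove recovery of lesion-specific ischemia.** The documents do not support that. The aim in the Abstract and the objectives in section 2.2 concern coronary physiology and dose–response, and require no proof by type. The implication for lesion-specific patients is worded as a possible future one, and the article calls for larger trials first. The sentence that both values can rise is a hypothesis in the Discussion, not a declared co-primary claim.
- **A reader might infer that the trial would have no lesion-level evidence.** That is also wrong. ΔFFRCT is a secondary endpoint, and section 2.8 records lesion-specific values (where applicable) and terminal values in all vessels. What remains is that ΔFFRCT is a different metric from the primary one.
- **A by-type analysis may sit in the Supporting Information or the analysis plan, which are not shown.** Its absence from the article is therefore no finding. The point is limited to how the primary is fixed here against the hypothesis stated here.
- **A reader might infer from the exclusions in Table 1 that lesion-specific patients are fewer than half.** That is speculative. The earlier 50% already refers to patients deferred from catheterization, and every patient here has a stenosis of at least 50%. Hence the two-sided range of 30% to 70%.

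**Conclusion.** The point holds in limited form and is minor. On the natural reading, a significant primary result supports an average rise in FFRCT and leaves open which type rose. The gap is wide for change over time: a positive test has 86% to more than 99.9% probability with no lesion-specific change at all. For the arm comparison it is smaller, at 18% to 68%, but still well above 5%. These figures rest on the assumed shares, two-sided 5% and SD 0.03. They also carry section 2.11's effect sizes, which rest on nine patients and the lowest distal value, over to patients measured 2 cm beyond the stenosis. The plan's stated power is not in dispute. Nor do the documents support saying that the endpoint is invalid, or that the trial cannot inform on lesion-specific disease.

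**What to change.** 1. Reconcile the Abstract with section 2.10, and state whether components (1) and (2) form one test or two.
2. In section 2.12 keep the overall test, but include baseline ischemia type in the model. This also takes the difference in mean change between types out of the error term.
3. As supportive estimates, report the 18-month change and the arm difference for each type with 95% CIs, together with the type-by-arm interaction.
4. Base any statement about lesion-specific ischemia on the lesion-specific estimate. Claim that both types improve only if both intervals exclude zero. Otherwise, limit the conclusion to the average over the pooled population.

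Cost: a few lines of text. Type is already fixed at baseline by the endpoint definition, so no new data or patients are needed. The downside is wider intervals by type. At 31 patients of one type, the power for the arm difference is only about 63%, so an interval that includes zero should not be read as evidence of no effect.
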